## Abstract

**Background:**

Autism entails reduced communicative abilities. Approximately 30% of individuals with autism have intellectual disability (ID). Some people with autism and ID are virtually non-communicative and unable to notify their caregivers when they are in pain. In a pilot study, we showed that heart rate (HR) monitoring may identify painful situations in this patient group, as HR increases in acutely painful situations.

**Objectives:**

This study aims to generate knowledge to reduce the number of painful episodes in non-communicative patients’ everyday lives. We will 1) assess the effectiveness of HR as a tool for identifying potentially painful care procedures, 2) test the effect of HR-informed changes in potentially painful care procedures on biomarkers of pain, and 3) assess how six weeks of communication through HR affects the quality of communication between patient and caregiver.

**Methods:**

We will recruit 38 non-communicative patients with autism and ID residing in care homes. *Assessments*: HR is measured continuously to identify acutely painful situations. HR variability and pain-related cytokines (MCP-1, IL-1RA, IL-8, TGFβ1, and IL-17) are collected as measures of long-term pain. Caregivers will be asked to what degree they observe pain in their patients and how well they believe they understand their patient’s expressions of emotion and pain. *Pre-intervention:* HR is measured 8 h/day over 2 weeks to identify potentially painful situations across four settings: physiotherapy, cast use, lifting, and personal hygiene. *Intervention:* Changes in procedures for identified painful situations are in the form of changes in 1) physiotherapy techniques, 2) preparations for putting on casts, 3) lifting techniques or 4) personal hygiene procedures. *Design:* Nineteen patients will start intervention in week 3 while 19 patients will continue data collection for another 2 weeks before procedure changes are introduced. This is done to distinguish between specific effects of changes in procedures and non-specific effects, such as caregivers increased attention.

**Discussion:**

This study will advance the field of wearable physiological sensor use in patient care.

**Trial registration:**

Registered prospectively at ClinicalTrials.gov (NCT05738278).

## Background

Social communication deficits are among the core features of autism spectrum disorder (ASD) [1]. Symptoms and support requirements for ASD vary in form and intensity with communication deficits ranging from mild to severe [2]. Approximately 30% of people with an ASD diagnosis also have intellectual disability (ID) [3], a neurological condition that affects 1% of the population [4, 5]. For low-functioning individuals with ASD or ID, the symptoms often overlap, and clear-cut diagnosis constitute a challenge [6–8]. The diagnosis of ID involves an intelligence quotient (IQ) below 70, reduced adaptive behaviour, and occurrence of the condition before the age of 18 [1, 8]. Approximately 5% of those with ID have grade severe (IQ: 20–34) or profound (IQ < 20) and need round-the-clock supervision and help [9, 10]. Although ID can be an acquired condition, for instance due to cerebral hypoxia, ischemia or infection early in life [11–14], genetic conditions, such as a de novo mutation [15], are a common cause. Severe or profound ID often coincide with cerebral palsy that affects control of muscles involved in speech, gesticulation, and grimacing. These patients with severe ASD and ID may be unable to notify their caregivers when they are In pain [16–20] and are essentially non-communicative.

There is a need to improve health services for non-verbal patients. Despite the rights of people with disabilities being enshrined in the UN Convention from 2006 [21, 22], age of death remains lower and mortality rates higher for people with intellectual and developmental disabilities [23, 24]. Patients with comorbid ASD and ID often have complex medical needs and many cannot convey their needs to their caregivers [25]. They will typically need the equivalent of 5–10 full-time staff per year–- a major challenge both in terms of competence needs and resource use [26]. Due to the demanding and person-intensive nursing attention required, there is considerable interest in technological solutions to aid communication and participation for this vulnerable group [27, 28]. Overall, technology can improve independence, participation and quality of life among people with complex needs [29].

Sensors may be used to monitor physiological parameters and activity patterns so that individuals and their caregivers can learn about their health. As a neurally mediated phenomenon, heart rate (HR) is regarded a noninvasive window into the central nervous system [30]. Changes in HR are widely used as markers of reactivity to painful events [30–37], and clinically HR is used in neonatal pain assessment and care [31]. Pain is an inferred latent process associated with several physiological and psychological markers including changes in neural activity as measured by electroencephalogram (EEG), pupil dilation, skin conductance, HR, blood pressure, and respiration, as well as self-reported pain magnitude [38, 39]. Although pain-induced increases in blood pressure may trigger vagal baroreflexes that counteract sympathetically-mediated tachycardia; sympathetic changes are found to dominate [40], making HR a reliable non-invasive way to identify probable painful events [40–42]. Although the central nervous system, cardiovascular system, and pain are closely interrelated [43, 44], HR is not a specific indicator of pain [30]. States like depression, being tense, angry or frightened may also involve an increase in HR due to a release of stress hormones like cortisol and adrenaline. The clinical application of such reactivity is shown in studies using HR to predict acute stress in ASD [45, 46]. As a more general reactivity measure HR is promising as a tool, and when context is given, it may be useful in non-verbal patient pain-management.

We have previously shown that HR can be used as a person-specific measure of reactivity for non-verbal patients [47]. To evaluate HR as a tool to assist pain management for non-verbal patients, other well-established biomarkers of pain, such as heart rate variability (HRV) and cytokine biomarkers in blood, should be utilized. HRV is a non-invasive measure of imbalances in the autonomic nervous system with a higher variance indicating less stress [48, 49]. A growing body of psychological research has shown HRV to be a stable biomarker of prolonged pain [50], and research supports an association between HRV and emotional responses [51, 52]. Recent studies suggest that certain circulating inflammatory cytokines can be utilized as reliable biomarkers for detecting chronic pain in various diseases [53–55]. Blood biomarkers of pain include MCP-1, IL-1RA, IL-8, TGFβ1, and IL-17 [53–55]. Elevated levels of these cytokine biomarkers have been associated with experimental pain and self-rated pain, and their levels have been shown to closely follow the temporal phenomenology of pain episodes [54]. The combination of HR, HRV and cytokine biomarkers may prove a novel tool for pain assessment.

Despite the potential of this approach, the use of sensors in care for non-verbal patients is not yet widespread. Most studies on sensors for pain management and communication has been conducted among patients with an ability to communicate [48, 56–60]. Non-verbal patients are frequently left out of research studies, even though advancements in medical technology could bring significant benefits to this patient population.

The proposed study is a randomized controlled trial that seeks to reduce incidence of pain for non-verbal individuals with autism and ID through use of HR-sensors. This study aims to 1) assess the effectiveness of HR as a tool to identify potentially painful care procedures; 2) test the impact of HR-informed changes on pain biomarkers; and 3) examine the impact of six weeks of HR monitoring on the quality of communication between patients and caregivers.

## Methods

### Study design overview

This is a single centre, controlled, randomized trial with 38 non-verbal participants, testing if HR-guided interventions in suspected painful settings will change the incidence of pain. The study design includes a two-week *pre-intervention*, consisting of continuous HR registering across four potentially painful settings; and an *intervention phase* consisting of formal change in procedure for the identified painful situation (Fig. 1). The interventions are in one of four forms: changes in 1) physiotherapy techniques, 2) preparations for putting on casts, 3) lifting techniques or 4) personal hygiene procedures. HRV and inflammatory cytokines (MCP-1, IL-1RA, IL-8, TGFβ1, and IL-17) are measured at the beginning, midway, and end of the study period to assess change in long-term pain. Participants will be randomly assigned to either an early intervention group or a delayed intervention group in a 1:1 ratio using a computer-generated randomization scheme. This will differentiate the effect of formal change in routine from increased attentiveness due to study participation, and instant changes made when the HR band signify obvious acute pain (such as skin pinched while putting on a cast). Overview over measures and objectives is given in Table 1.

**Fig. 1 Fig1:**
[figure not shown]
Overview of phases in a clinical study. Abbreviations: HR: heart rate, HRV: heart rate variability, NCPC: Non-communicating Children’s Pain Checklist; NCAPC: Non-Communicating Adult Pain Checklist

**Table 1 Tab1:** Timeline of trial illustrating the timing of different biomarkers and data collection, as well as their corresponding hypothesis

Timepoint	T0		T1		T2	
Nr. Week	1	2	3	4	5	6
Early group	Pre-intervention phase^a^		Change in care procedure			
Delayed group	Pre-intervention phase^a^				Change in care procedure	
Time of samples collected and corresponding hypothesis						
*Primary hypothesis*	HR↑ + context	HR↑ + context	HR↑ + context	HR↑ + context	HR↑ + context	HR↑ + context
*1*^*st*^* Secondary*	HR↑	HR↑	HR↑	HR↑	HR↑	HR↑
	Cytokines			Cytokines		Cytokines
	HRV			HRV		HRV
2^nd^* Secondary*	CU^b^					CU^b^

^a^Registration of HR increases in potentially painful situations in the patient’s everyday life

^b^Caregivers’ rated understanding of the patient as measured by a trial-specific survey, given in Table 4

*Abbreviations*: *TG* Treatment group, *DG* Delayed intervention group; HR↑ = Heart rate increases; Context = Contextual data; Cytokines = MCP-1, IL-1RA, IL-8, TGFβ1, and IL-17; HRV = heart rate variability; metabolites; CU = ^b^Caregiver’s rated understanding

### Objectives

The overarching aim is to generate knowledge to reduce incidence of pain in non-verbal patients’ everyday lives.

#### Primary objective

The primary objective is to evaluate how HR as measure of patient reactivity can be used to identify potentially painful care procedures that should be re-evaluated in terms of the approach taken.Primary hypothesis:* HR increases as defined by 2 standard deviations (SD)*
*increase in HR can identify potentially painful care situations in the patient’s everyday life that that should be re-evaluated (e.g., different methods for stretching of spastic limbs, different routines for transport with personal lifts).*

#### Secondary objectives

The secondary objectives are to:

Evaluate how HR-informed changes in potentially painful procedures affect pain biomarkers.

*Secondary hypothesis 1: HR-informed changes in patient-specific care procedures (a. physiotherapy, b. applying cast for spastic limbs, c. transportation/being lifted, or d. routines for personal hygiene) will increase HRV and reduce pain-related cytokines (MCP-1, IL-1RA, IL-8, TGFβ1, and IL-17) as evaluated at the beginning, mid-way and at the end of the study period.*

2)Assess how six weeks of communication through HR affects the quality of communication between patient and caregiver.

*Secondary hypothesis 2: HR as an aid in communication will increase caregivers’ understanding of the patient as measured by changes in perceived understanding of the patient from the beginning to the end of the study period.*

### Study design

#### Intervention

The intervention comprises individualized routines to reduce pain in potential pain-inducing settings.

In the pre-intervention phase, HR is continuously collected for 8 h/day across potentially painful care situations. The primary caregiver will report on situations with an HR increase (Figs. 4 and 5).

As the caregiver is not blinded to the HR increases during the registration phase, we expect instantaneous changes made when the HR band communicated obvious acute pain (e.g. skin pinched while putting on cast). These instantaneous, non-formalized changes made by each caregiver is not regarded as “change in routine” but are registered as HR-informed adaptations. The intervention consists of a formal change in routine, and involved changes is written routine and training of staff for the chosen situation. Allocation into an early group and a delayed group helps distinguish the non-formal adaptations based on HR from the effect of formal changes in procedures of care.

Based on the two-week pre-intervention phase, one of four types of care procedures are chosen as the intervention target: 1) physiotherapy, 2) applying cast on spastic limb, 3) transportation/being lifted and 4) personal hygiene procedures. If there are several situations identified as candidates for intervention, selection will be based on a) level of reproducibility and b) magnitude of HR increase. The procedure must be easily recognizable. The situation should at have an HR-spike occurrence for at least 10 episodes during the recording period (i.e. on average 1 occurrence/day), with at least 80% of the situation resulting in HR-increase (reproducibility).

The intervention will be in one of four forms:changes in physiotherapy, e.g., less rigorous movement in the identified painful stretch,preparations for putting on corrective cast to stabilize joint and/or stretch spastic muscles,change in procedures for transportation/lifting, e.g., new technique or adjustments made to equipment, orrevised personal hygiene procedure.

If none of the predefined interventions fit the chosen stressor, a fitting intervention is constructed and will be described separately and in detail when the results of this study are published.

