#### Method of assigning participants to treatment groups

The study design employs an early and a delayed intervention group to distinguish the effects of formal routine changes from increased attentiveness due to study participation and effects of instantaneous changes in care. The early intervention group will start intervention in week three while the delayed group will continue data collection for another two weeks before introducing procedure changes. Patients will be randomly assigned to one of the two groups (Fig. 1) on a 1:1 ratio using a computer-generated randomization scheme.

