#### Analysis of primary objectives

We hypothesize that a 2 SD increase in HR can identify potentially painful care situations that require re-evaluation. To determine whether HR monitoring is effective in identifying situations that require changes in care, we will compare the mean HR spike counts between situations that are suitable for adjustments in care versus situations that are not. If Shapiro–Wilk test show normality of data distribution, we will use a one-tailed paired sampled t-tests; if non-normality is indicated we will use the Wilcoxon signed-rank test.

The potential for HR to identify potentially painful care procedures will also be shown as descriptions of identified situations and shown as a number count (primary hypothesis). All situations identified by 2 SD increase in HR will be described and reported as count, including an overview of number of times each of the different situations were accompanied by increases in HR (reproducibility); number of HR increases with no registration (responsiveness of caregiver); number of HR increases recorded in situations not previously thought to entail pain or distress (novel discoveries); number of situations discovered through HR-use during the registration phase where instantaneous changes were made due to obvious acute pain (e.g. skin pinched while putting on cast; instantaneous clinical effect of HR); and number of situations identified that were available for adjustments in care and systematic evaluation (formal clinical applicability of HR).

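### The chosen target's reproducibility is biased upward in the weeks that selected it, and the plan neither fixes a reporting window nor uses the delayed arm's weeks 3-4 for a post-selection estimate

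*Protocol article*

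**What the plan says.** **Selection.** The protocol's Intervention section states: "Based on the two-week pre-intervention phase, one of four types of care procedures are chosen as the intervention target". A situation qualifies with an "HR-spike occurrence for at least 10 episodes during the recording period". It must in addition meet a condition on the rate, worded as "with at least 80% of the situation resulting in HR-increase (reproducibility". If several qualify, "selection will be based on a) level of reproducibility and b) magnitude of HR increase". The section on discontinuing or modifying interventions repeats the 10-episode rule for the same two weeks. It adds that patients without a target stay in the final presentation, to show in what share of patients heart rate can guide formal change.

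**Reporting.** Under Analysis of primary objectives the plan says: "All situations identified by 2 SD increase in HR will be described and reported as count". One of the outputs it lists there is the "number of times each of the different situations were accompanied by increases in HR (reproducibility". The same list ends with a count of situations open to formal adjustment, offered as the formal clinical applicability of heart rate. No time window is given for any of these outputs.

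**Data available.** Table 1 lists heart-rate increases with context under the primary hypothesis in all six weeks. It shows no procedure change in the delayed group until week 5. The section on assigning participants says that "the delayed group will continue data collection for another two weeks before introducing procedure changes". The stated purpose of that group is to separate formal change from attention and informal adaptation. Re-estimating a target's reproducibility is not mentioned.

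**The concern.** A rate that has to exceed a cut-off before a procedure is chosen overestimates that procedure's underlying rate when it is read from the same observations. Procedures that spiked more often than usual in those two weeks are more likely to be chosen, and the preference for the highest rate works in the same direction. If that rate is later offered as evidence that heart rate reproducibly identifies procedures needing re-evaluation, part of it is produced by the selection rule.

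The delayed arm supplies two more weeks after selection and before formal change. A rate from those weeks is not conditioned on having passed the rule. The itemised list of primary-objective outputs leaves it out, although the data are collected anyway.

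**Working it through.** **1. The plan's own figure.** There is none to reproduce. The protocol gives no expected reproducibility, number of performances per fortnight or size of selection effect. The inputs below marked as assumed are not in the document.

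**2. Inputs.**
- From the Intervention section: at least 10 spikes, at least 80%, highest rate first, selected on two weeks.
- Assumed: n = 12, 14, 20 or 28 performances per procedure in two weeks; up to four procedures per patient; binomial spikes with an unchanging true rate p.

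**3. What the rule requires.** The required count is the larger of 10 and 0.8n rounded up: 10 of 12, 12 of 14, 16 of 20, 23 of 28. The chance that one procedure passes is P(X ≥ required count), with X ~ Binomial(n, p):

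| n | p = 0.7 | p = 0.8 | p = 0.9 |
|---|---|---|---|
| 12 | 0.253 | 0.558 | 0.889 |
| 14 | 0.161 | 0.448 | 0.842 |
| 20 | 0.238 | 0.630 | 0.957 |
| 28 | 0.113 | 0.501 | 0.945 |

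With four procedures all at 0.7, at least one passes with probability 1 − (1 − 0.253)^4 = 0.69 for n = 12. The corresponding values are 0.50, 0.66 and 0.38 for n = 14, 20 and 28.

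**4. Bias of the chosen target's rate.** Simulation of 200,000 patients per scenario: apply the rule, take the highest rate among four procedures, and compare the observed with the true rate. Ranges run over the four values of n.

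| Assumed true rates | Bias (points) | Meets the rule again in a fresh window |
|---|---|---|
| Uniform 0-1 | 3-6 | 75-83% |
| Uniform 0.5-0.95 | 4-8 | 67-79% |
| Beta(2,2) | 5-10 | 56-67% |
| All 0.9 | 5-8 | 84-96% |
| All 0.8 | 8-12 | 45-63% |
| All 0.7 | 14-19 | 12-25% |

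Example: n = 14, Beta(2,2). Chosen targets show 91.3% against a true 82.1%, a bias of 9.2 points. The bias is upward in every scenario.

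**5. Source of the bias.** With true rates uniform on 0-1, the bias is 3-6 points whether one, two or four procedures compete. In that setting the 80% cut-off produces it, and choosing the best of four adds little.

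**6. What failing on repeat means.** Across spread-out scenarios (including uniform 0.3-0.9 and 0.2-1.0), 16-48% of chosen targets fail the rule in a fresh two weeks. A procedure with a true rate of 85% also fails 26%, 35%, 17% and 24% of the time (n = 12, 14, 20, 28). One at exactly 80% fails 1 − 0.630 = 37% to 1 − 0.448 = 55% of the time.

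**7. Patients available.** 19 in the delayed arm; 19 × (1 − 0.15) = 16.15, so about 16 after the allowed dropout, and fewer where no target qualifies.

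**The case against.** **The window.** A reader might infer that the reported reproducibility is computed from the same two weeks that chose the target. The document does not say so. The primary-objective section gives no window, and Table 1 lists heart rate with context for all six weeks. The Fig. 5 caption, which places trigger registration in the pre-intervention phase, and the shared term reproducibility point towards weeks 1-2, but only as an inference. This stands. What can be faulted is that the window is left open. Pooling all six weeks would not help, because it would mix the selection window with weeks after formal change.

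**The scope.** The plan reports every identified situation, not only the chosen target, and nowhere makes the target's rate a headline figure. This also stands. The at-least-80% floor applies only to chosen targets, so it would go too far to say that the trial's main descriptive claim is overstated.

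**Weeks 3-4.** They might be read as an unchanged replicate. They are free of formal change only. The Intervention section and the Discussion expect caregivers to adapt at once to obvious acute pain, so a lower rate would mix regression to the mean with adaptation.

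**Chance selections.** Failure on repeat might be read as showing that the target was chosen by chance. Step 6 of the working shows that procedures genuinely above 80% fail often too. The most alarming figures need every procedure in every patient to sit at 70%, for which the document gives no support.

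**Importance.** The figure is descriptive, and correcting it changes no test, allocation or sample size. A condensed article may also leave the window of a descriptive table to a fuller document. That limits the weight of the point. It does not remove the selection effect or the value of two post-selection weeks already being recorded.

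**Conclusion.** The point holds in a limited form. The chosen target's weeks 1-2 reproducibility is biased upward by about 3-10 points under spread-out true rates and 12-28 performances, 8-12 points if all true rates equal 0.8, and 14-19 points if all equal 0.7. The direction follows from the selection rule. The size rests on assumed performance counts, assumed true rates and independent binomial spikes. The protocol leaves the reporting window open and plans no analysis of the target in the delayed arm's weeks 3-4.

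Treating those weeks as post-selection assumes that the delayed arm's target is fixed on weeks 1-2, as the Intervention section says. The documents do not support saying that the reported figure is certainly from the selection weeks, that weeks 3-4 are an exact replicate, or that targets failing on repeat were chance selections. This is a cheap improvement to how the usefulness of heart rate is described, and it does not affect the validity of a hypothesis test.

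**What to change.** Under Analysis of primary objectives:

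1. State the weeks from which reproducibility is computed.
2. Label the chosen target's weeks 1-2 rate as the selection value.
3. For the delayed arm, report the target's weeks 3-4 rate separately, with a confidence interval that treats the patient as the unit, and the proportion of targets that meet the rule again.
4. Show these results with and without targets that had a registered informal adaptation.
5. Call the result a post-selection estimate, not a confirmed figure. Say that a fall may reflect regression to the mean, informal adaptation or both, and that failure to meet the rule again does not prove a chance selection.

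The selection rule itself and patient care are untouched. The cost is one further descriptive analysis of data already planned. The downside is a small base (at most 19 patients, about 16 after dropout, fewer where no target qualifies), hence a wide interval, and a less favourable figure.
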